##### Knowledge and skills

The Brief Illness Perception Questionnaire (B-IPQ) will be used for measuring illness beliefs [42, 43]. B-IPQ contains 9 nine items of which each covers one construct: consequences, timeline (expectations of prognosis), personal control, treatment control, identity (extent of symptoms), coherence (understanding of symptoms), emotional representation, concerns, and cause. Based on the properties of the scale observed in the pilot project, we expect to combine ‘consequences’, ‘identity’, ‘concerns’, and ‘emotional representation’ into ‘Interference’ (sum score 0–40), ‘personal control’ and ‘coherence’ into ‘Coherence and Control’ (sum score 0–20), and ‘timeline’ and ‘treatment control’ into ‘Expectations’ (sum score 0–20). If the internal consistency allows it, a sum score of items 1–8 will then be calculated as a measure of overall illness perceptions (0–80).

Perceived ability to perform exercises is measured by one question: ‘How confident are you in performing exercises in a beneficial way?’ (0–10 scale from ‘not confident at all’ to ‘absolutely confident’).

The four physical performance tests are: sit-to-stand test (number of repetitions in 30 s) [44, 45]; standing forward bending (0: No forward bending; 1: pain and restricted movement; 2: no pain and restricted movement; 3: pain and unrestricted movement; 4: no pain and unrestricted movement) [46–48]; iso-extensor endurance test (seconds in static position up till 3 min) [49, 50]; trunk flexor endurance test (seconds in static position up till 2 min) [50, 51]). All these tests are affected in chronic LBP, and the sit-to-stand test, extensor endurance and standing forward bending have been demonstrated to be responsive to change [52, 53].

##### Beliefs and performance

The B-IPQ ‘Expectations’ subscale measures recovery beliefs and the Fear Avoidance Beliefs Questionnaire physical activity scale (0 = no fear avoidance beliefs; 24 = highest possible fear avoidance beliefs) will be used to measure fear of movement [54–56].

Self-assessed physical fitness visual analogue scales compare perceived strength, endurance, flexibility, and balance with that of other people of the same age and sex and is used for measuring physical fitness [57, 58]. To capture the goal of moving freely we will add one item to self-assessed physical fitness and ask to what extent the patient perceives her−/himself ‘moving unhindered and naturally’.

##### Self-efficacy

The Arthritis Self-Efficacy Scale (ASES), subscales of pain and other symptoms will be used to assess symptom self-efficacy [59]. The ASES includes five items on pain and six on other symptoms. The scale was developed for arthritis but has also undergone validation also in a mixed group of patients with chronic pain [60] and in patients with fibromyalgia [61]. The questions ask about the degree of certainty that the respondent can manage with respect to aspects around pain, sleep, fatigue and mood. Each item is scored on a 0–10 scale (0 = very uncertain; 10 = very certain). For our purposes ‘arthritis’ will be changed to ‘back pain’.

##### Self-management success

The Oswestry Disability Index [62, 63], work ability (‘Imagine your ability to work is worth 10 points at its best. How many points will you give your current work ability?’ (0–10), LBP intensity (Numeric Rating Scale 0–10 [64]), quality of life (SF-36 subdomains of general health, social functioning, mental well-being), pain interference with life (B-IPQ ‘interference’), and achieved individual goal (SMART 0 = Not achieved at all - 10 = Fully achieved [40]) will be used to measure the success of self-managing pain. Because there is not one specific measure for this construct, other authors have suggested capturing a range of constructs including pain-related disability, pain intensity, quality of life, perception of social support, self-efficacy, pain acceptance, depression, anxiety, and general health as outcome measures of self-management interventions [65, 66].

##### System outcomes

Health care utilisation data (number of visits to GP, chiropractor and physiotherapist, prescription of pain medication, referrals to spine imaging, and referrals to secondary care for back pain) will be extracted from the Danish National Health Service Registry [67]. In addition, patients will be asked about care-seeking due to LBP and use of pain medication for LBP. Long-term sick leave (number of days off work after 1 month of absenteeism) is available in the ‘DREAM’ registry from the Ministry of Employment [68].

##### Patient characteristics

Age, sex, socio-economic status (education, job, income), LBP history (duration, recall of 1-year trajectory, previous care), and results from the Start Back Screening Tool (low, medium and high risk of poor prognosis) [69] will be collected at baseline in addition to the outcome measures mentioned above.

#### Outcomes of the clinician educational intervention

An overview of the study measures is provided in Table 5.

**Table 5 Tab5:** Overview of study measurements related to the educational intervention targeted at clinicians

Construct	Instrument	Course registration	Before course	After course	5-months	Patient baseline registration	Patient reported at 3-months
Individual characteristics	Age, sex, profession	x					
Experience	Years of clinical experience Experience with GLA:D for knee and hip	x					
Clinic characteristics	Workplace (Private clinic, municipality, secondary care) Number and professional background of clinicians in the workplace	x					
Treatment orientation	The Pain Attitudes and Beliefs Scale for Physiotherapists [70–72]		x		x		
Confidence and capability	The Practitioner Confidence Scale [73] + 2 added items The Determinants of Implementation Behaviour Questionnaire (knowledge, skills, beliefs about capabilities) [74]		x		x		
Motivation	The Determinants of Implementation Behaviour Questionnaire (Beliefs about consequences, innovation, patients, intentions) [74]			x	x		
Opportunity	The Determinants of Implementation Behaviour Questionnaire (organisation, social influences, social context, and behavioural regulation) [74]			x	x		
Delivery of key messages	Patients asked to what extent they during the course of care they have heard about key messages of GLA:D Back (e.g. that pain does not signal harm) and messages contradictory to GLA:D Back (e.g. that certain positions or movements have to be avoided)						x
Establishing individual goals	SMART value-based goal registered at the initial consultation					x	

##### Outcomes related to learnings

The Pain Attitudes and Beliefs Scale for Physiotherapists (PABS-PT) is a self-administrated questionnaire developed to assess the strength of two possible treatment orientations of physiotherapists toward the management of back pain: predominantly biomedical orientation or predominantly behavioural orientation [70, 71]. We will use the 19-item version and added two questions based on a recent Rasch analysis of the Norwegian PABS (‘If ADL activities cause more back pain, this is not dangerous’; ‘Reduction of daily physical exertion is a significant factor in treating back pain’) [72]. The resulting biomedical subscale will consist of 11 items (sum score 11 to 66) and the behavioural subscale of 10 items (sum score 10 to 60).

The four-item Practitioner Confidence Scale (PCS) measures clinicians’ confidence in managing people with back pain [73]. Two items will be added to capture confidence about using a behavioral pain model (‘I feel confident using psychological and behavioural elements in the treatment of LBP patients’ and ‘I feel confident working with patient with LBP not basing this on a structural diagnosis’). Each item is scored on a five-point scale from 1 = ‘strongly agree’ to 5 = ‘strongly disagree‘, resulting in sum scores ranging from 6 to 30.

The Determinants of Implementation Behavior Questionnaire (DIBQ) will be used to measure the domains of knowledge, skills and capabilities about the delivery of GLA:D Back [74]. The DIBQ was developed from the Theoretical Domains Framework and covers 18 domains related to implementation processes [16]. We will include 31 items from the domains of knowledge (2 items), skills (1 items), beliefs about capability (6 items), beliefs about consequences (4 items), innovation (4 items), patients (2 items), intentions (1 item), organisation (2 items), social influences (3 items), social context (1 item), behavioural regulation (3 items), and innovation strategy (2 items). Items are scored 1 = strongly disagree to 7 = strongly agree, with negative statements reverse-coded.

##### Outcomes related to clinician behaviours

The delivery of a group-based patient education and exercise program will be assessed as the proportion of patients who reports participation in both of these activities. The delivery of key messages as part of the intervention will be measured as patients’ recall of having heard five key messages as part of their treatment course. Three of the listed messages are key messages in the GLA:D Back approach (‘Movement is healthy for the spine’, ‘Pain does not equal harm’, ‘Your brain has a memory for pain – like having a bad song stuck in your head’) and two are messages not in line with the intention of GLA:D Back (‘I need to avoid certain positions or movements’, ‘In my case, pain means I should stop what I am doing’). Both measures of delivery of care are included in the patient three-month follow up. Use of individual goals will be measured as the proportion of patients for whom a goal is described in the clinical registry.

#### Clinician and clinics characteristics

Information will be collected to describe clinician profiles: age, sex, profession, years of clinical experience, type of employment, experience with GLA:D knee and hip, and whether or not their clinical work is conducted under a contract with public health insurance. Information will also be collected about clinics: the number of physiotherapists, chiropractors, massage therapists and other clinicians in the clinic, whether GLA:D for knee and hip is offered, and if back pain group exercises were offered before introducing GLA:D Back.

#### Outcomes related to the national implementation

##### Promotion activities

Promotion of the course will be measured via the number of times GLA:D Back is mentioned in social media postings, newsletters and magazines (Table 2).

##### Reach, adoption and penetration

Clinician reach will be quantified as the number of clinicians signing up for the GLA:D Back courses, rate of adoption as the proportion of these who enrol patients in the program, and geographical dissemination as the extent of spread across the country (Table 3). The profiling of clinicians will include years of clinical experience, sex, profession (physiotherapist, chiropractor), place of employment (municipality, primary care clinic, secondary care), type of employment (clinic owner, employee, self-employed in a clinic owned by another person).

##### Fidelity

The outcome measures listed above about clinician behaviours are measures of fidelity.

##### Determinants of implementation

The DIBQ domains that relate to national implementation are organisation, social influences, social context, and behavioural regulation.

##### The profile of patients enrolled

Using data concerning the patient characteristics collected above, we will be able to profile patients enrolled in GLA:D Back.

##### Acceptability among patients

Clinicians will be asked ‘What proportion of invited patients would you say join GLA:D Back?’ (< 25%, 25–50%, approx. 50%, 50–75, > 75%), and ‘What are the main reasons why patients decline participation?’ (price, time point, don’t want supervised training, don’t want patient education, find the program too comprehensive, other reasons). If the last individual session does not occur, clinicians will report if the patient otherwise completed the intervention (Program completed without final session; Program not completed). Compliance with the program will be registered as the number of education sessions and exercise sessions patients report they attended when completing the three-months follow up.

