### Interventions

#### The GLA:D Back clinical intervention

This clinical intervention is intended for people with persistent or recurrent low back pain (LBP) and in need of improved self-management. The content and intervention mapping are presented in detail elsewhere [30]. Briefly, GLA:D Back consists of an individual session of clinical testing and goal-setting at the beginning and end of the program, two one-hour group sessions of patient education, and 8 weeks of twice-weekly one-hour supervised exercises sessions (Fig. 2).

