There are no strict patient inclusion criteria, and the decision to enrol a patient in GLA:D Back is at the discretion of the clinician in a dialogue with the patient, when clinicians judge that the patient would benefit from improved self-management skills. Patients can be enrolled at the first visit or later depending on whether individual treatment sessions are deemed necessary prior to starting GLA:D Back. When patients begin the program their contact information is entered in the clinical registry, which in turn activates links to patient questionnaires that are sent automatically on the day of registration and again after 3, 6 and 12 months. Clinicians enter results of physical tests and patients’ individual goals in the registry before patients start the GLA:D Back intervention and when the program ends. The price and out-of-pocket expenses for the GLA:D Back intervention can vary between clinics and types of insurance.

Consultants for physiotherapy, chiropractic, and family medicine working with primary care in the five administrative regions were invited to an information meeting about GLA:D Back before course registration was opened (January 2018). Family physicians will be informed through professional journals and seminars.

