### Effectiveness and process evaluations

#### Data collection

Data sources will include: 1) data obtained from clinicians when they register for a GLA:D Back course, 2) clinician-completed surveys before and directly after the course and after 5- months, 3) observations of patient education and exercise group sessions in selected clinics, 4) patient physical tests at baseline and at the end of treatment, 5) patient-completed surveys at baseline, 3-months, 6-months and 12-months, 6) patient interviews, and 7) information from Danish registries (Fig. 5). Patient and clinician data are collected electronically using the REDCap software (Vanderbilt University) provided and supported by the Odense Patient data Explorative Network (OPEN) [41].

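### Goal attainment and the physical re-tests appear to depend on a final clinician session that may not take place, so both are open to selection bias of unknown size and direction

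*Protocol article*

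**What the plan says.** The section on self-management success lists six kinds of measure, among them "achieved individual goal (SMART 0 = Not achieved at all", rated up to 10 for full achievement. The other five are disability, work ability, pain intensity, three SF-36 domains and illness interference.

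The programme includes "an individual session of clinical testing and goal-setting at the beginning and end of the program" (The GLA:D Back clinical intervention). The national implementation section has clinicians enter test results and patients' goals "in the registry before patients start the GLA:D Back intervention and when the program ends". The data collection section likewise lists "patient physical tests at baseline and at the end of treatment". Table 4 shows the four tests as clinician-reported, before and after the intervention only.

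Patient questionnaires follow a different route: their links are "sent automatically on the day of registration and again after 3, 6 and 12 months", whether or not the final session is held.

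For the case "If the last individual session does not occur", the section on acceptability among patients has the clinician choose between two statuses: "Program completed without final session; Program not completed". It mentions no substitute for the goal rating or the tests.

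The section on evaluating the clinical intervention defines its population as the patients in the GLA:D Back registry, that is, everyone enrolled.

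**The concern.** Two measures have a capture point that depends on the patient's own course through the programme. A patient who stops early, or finishes the exercises but skips the closing session, would contribute neither a goal rating nor a re-test. Patients who miss that session may well differ from those who attend in what they achieved, so a mean over attenders need not describe the enrolled population.

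For goal attainment, a listed success measure would be reported for a selected group. For the physical tests, improvement is also an early explanatory step in the planned mediation analysis, so the same selection would carry into that model.

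This arises at data capture. A rating that was never asked for can later be imputed or weighted only under an assumption about non-attenders that those data cannot test.

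**Working it through.** The protocol gives no figure on this point, so there is none to reproduce. The check has two parts.

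**Where each measure is captured**

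- *Physical tests.* Clinician-recorded before and after the programme (Table 4; data collection). The route is explicit.
- *Goal rating.* Table 4 has no row for it. Table 5 lists only the registration of a goal at the initial consultation, and the section on clinician behaviours counts only whether a goal is described. The likely route is the clinician's end-of-programme goal entry, but this is an inference.
- *Disability, work ability, pain, SF-36 domains, illness interference.* Patient-reported at baseline, 3, 6 and 12 months by automatic survey. They do not depend on the final session.
- *Stated fallback if the final session is missed.* Completion status only. Even a patient classed as having completed may therefore lack both measures.

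**Size of a possible bias**

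Let q be the share without a final session, A the mean in attenders and N the mean in non-attenders. The mean over all enrolled patients is (1 − q)A + qN. The attender mean differs from it by

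A − [(1 − q)A + qN] = q(A − N).

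The protocol gives neither q nor A − N. All values below are assumptions. The first three result columns concern the 0–10 goal rating. The last three are in standard deviations (SD) of change on a physical test.

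| q | gap 1 point | gap 2 points | gap 3 points | gap −0.2 SD | gap 0.2 SD | gap 0.5 SD |
|---|---|---|---|---|---|---|
| 10% | 0.1 | 0.2 | 0.3 | −0.02 | 0.02 | 0.05 |
| 20% | 0.2 | 0.4 | 0.6 | −0.04 | 0.04 | 0.10 |
| 30% | 0.3 | 0.6 | 0.9 | −0.06 | 0.06 | 0.15 |
| 40% | 0.4 | 0.8 | 1.2 | −0.08 | 0.08 | 0.20 |

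A gap of zero gives no bias at any q. A negative gap, for example if patients stopped because they had recovered, makes attenders look worse than the whole group. As a yardstick, the sample size section powers the pre-post comparison for an effect size of 0.2. Only the most adverse corner of the table (40% and 0.5 SD) reaches that value.

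**The case against.** The case against has real force, and several stronger readings fall to it.

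- *That the results will overstate improvement.* A reader might infer this, but the protocol gives no attendance rate, no attender/non-attender difference and no direction. Goal attainment is also a single end score, so it has no change from baseline to overstate; only its mean level could be too high.
- *That the final session will often be missed.* The text is conditional and gives no frequency. The intervention section makes the closing session a core part that clinicians may not alter.
- *That Table 4 proves the goal item is never put to patients.* Table 4 is an overview and is not exhaustive. Sessions attended, self-reported pain medication and income are all to be collected according to the text, yet have no entry there. Its silence on the goal rating shows that the rating is unscheduled, not that it is unasked.
- *That goal attainment cannot be related to later self-efficacy.* The mechanism plan attaches 6 and 12 months to the step from beliefs and capacity to self-efficacy. The step from self-efficacy to success has no stated time point, and an end-of-programme rating can be related to self-efficacy at any wave.

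The protocol also does part of the work. It profiles completers and non-completers, compares non-completion across clinician profiles and regions, and collects sessions attended. Those data could support weighting or imputation, and such handling belongs to the subproject analysis plans, whose absence here is no finding. Goals under the SMART model are time-bound, so scoring at programme end is defensible and repeats at 6 and 12 months would be a preference.

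What survives is narrow. For two measures the only described capture point appears to be the end-of-programme clinician entry, and nothing is stated to replace it when the session is missed.

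**Conclusion.** The point holds as a design weakness in two measures. As described, the goal rating (by inference) and the physical re-tests (explicitly) would be available essentially for patients who attend the final session, although the evaluation population is all registered patients. This creates a risk of selection bias. Overstatement is the plausible direction if non-attenders did worse, but the protocol does not show that they would.

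Under the assumed inputs the shift runs from 0.1 to 1.2 points on the goal scale for positive gaps of 1 to 3 points, and from −0.08 to 0.20 SD for the tests. These are illustrations, not estimates.

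The other five success measures are not exposed to this mechanism, so the evaluation as a whole is not undermined. The point still merits a change, because the goal rating can be collected independently of attendance at almost no cost and no later analysis could fully recover it.

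**What to change.** - Add a goal-attainment row to Table 4 with its source and time point, so that the listed success measure is scheduled.
- Ask the 0–10 item in the existing automated 3-month patient survey for all enrolled patients, displaying the goal stored in the registry. Keep the clinician's end-of-programme entry as a cross-check.
- Report physical-test change as a result in re-tested patients, giving the number re-tested out of all enrolled. These tests need attendance, so a survey cannot replace them.

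The cost is one table row, one survey item and the step that pulls the stored goal into the survey. Patients who do not answer the 3-month survey will still be missing, so the change removes the dependence on the final session but not ordinary non-response.

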##### Referrals and prescriptions

Suitable outcomes from national registries and population definitions for a pre-post comparison at the national level are still to be determined and will be informed by the characteristics of the population enrolled in GLA:D Back. Available information includes reimbursed visits to general practice, physiotherapists, and chiropractors, visits and diagnostic codes from hospital visits, referrals to reimbursed imaging and prescriptions of medication.

### Sample size

The study population will be the clinicians who complete GLA:D Back courses during 2018 and the patients enrolled in GLA:D Back by these clinicians during a 6-months window of inclusion commencing after a 3-month phase of familiarisation with the program after the course. Assuming that clinicians from 150 clinics will participate in the GLA:D Back course during 2018, and they enrol 1500 patients during the study period, we will have 90% power to demonstrate pre-post comparison changes at the patient level with an effect size of 0.2 while accounting for clustering within clinics and clinicians up to a variance inflation factor of 5. At the clinician level, we will have [75]90% power to demonstrate changes with an effect size of 0.27.

